## Abstract

**Background:**

Studies worldwide show insufficient blood pressure control rates, and effective management of hypertension remains a challenge in general practice. Although structured forms of care improved blood pressure in randomized controlled trials, little is known about their effects under routine primary care. This cluster randomized trial (CRT) evaluates the effects of a modern interactive medical education series for general practitioners on hypertension management, including practice redesign strategies.

**Methods/Design:**

For this CRT, 24 primary care academic teaching practices of the University of Duisburg-Essen, Germany, are randomized into two study arms. With the objective of improving hypertension control, general practitioners of the intervention group participate in a three-session medical education program on structured hypertension management. The program aims at changing physician awareness and practice design. Various practice tools are provided: for example, checklists on valid blood pressure readings, medication selection, detection of secondary hypertension, and patient education. General practitioners of both study groups include hypertensive patients with and without hypertension-related diseases such as angiographically proven coronary disease, and peripheral or cerebral vascular disease. Blood pressure is measured by 24-hour readings. Analyses will focus on differences in blood pressure control and changes of practice management between intervention and control group.

**Discussion:**

The study will determine the effectiveness of our practice redesign intervention on hypertension control. The intervention addresses general practitioners and practice assistants, while aiming at benefits on the patient level. Therefore, the cluster design is used to evaluate the effects.

**Trial registration:**

DRKS00006315 (date of registration: 14 July 2014).

## Background

According to a World Health Organization (WHO) report, hypertension is the single most important risk factor, accounting for 13% of mortality worldwide [1]. The EUROASPIRE III study documented that blood pressure control rates in patients with documented coronary artery disease averaged only 39% in eight European countries despite the availability of various therapeutic options [2]. A Cochrane review of 72 randomized controlled trials compared various interventions for controlling blood pressure: a complex intervention including patient recall systems and education aimed at overcoming physicians’ hesitancy to prescribe complex medication regimens was the best strategy, decreasing average systolic and diastolic blood pressure by 8.0 mmHg and 4.3 mmHg [3]. The randomized controlled Hypertension Detection and Follow-up Program (HDFP) study, which developed and applied this structured care for hypertensive patients, documented a significant decrease in mortality rates after 5 years: all-cause mortality in the intervention group was 17% lower than in the control group [4]. However, the challenge is still to translate these findings into routine care [3].

Internationally, primary care is delivered in various organizational settings ranging from one- or two-physician offices scattered in urban or rural areas to large-sized multi-physician practices and health maintenance organizations. Therefore, strategies to improve hypertension control are needed that are applicable in various clinical scenarios [3].

This cluster randomized trial evaluates the effectiveness of a modern medical education series for primary care physicians about structured hypertension management on blood pressure control in hypertensive patients. The intervention follows a modern didactic concept with evidence-based, interactive case discussions and practice redesign strategies. Primary care academic teaching practices are randomized into intervention group (education on hypertension management) and control group (no education).

## Methods/Design

### Study design

The study is designed as a cluster randomized trial with primary care practices as the unit of randomization. The cluster design is used because the intervention (education) addresses practice teams, and thereby aims to improve patient outcomes indirectly [5]. Additionally, this design takes into account that patients of a certain practice may be more homogenous regarding medical and sociodemographic characteristics than patients of other practices [5,6]. Each practice cluster includes five patients at minimum.

Practices from both arms will receive the intervention, but sequentially, with control practices receiving the intervention after the follow-up data collection in both study groups.

### Practice and patient recruitment

The study is conducted in the practice network of 180 primary care academic teaching practices of the University Duisburg-Essen, Germany. These practices are distributed in urban and rural regions of North Rhine-Westphalia with a distance of 5 to 150 kilometers to the Institute for General Medicine in Essen, Germany. All practices belong to the Association of Statutory Health Insurance Physicians North Rhine and Westphalia-Lippe. All practices are requested to take part in one of two network meetings of the institute yearly. Each practice is allowed to choose which meeting to attend: the spring or the fall meeting. All practices that participated in the spring meeting 2013 were asked to participate in this study (n = 51). Interested physicians are contacted by telephone to check practice inclusion criteria. Practices are eligible for participating in the study if they provide health services to hypertensive patients and are equipped with at least one calibrated 24-hour blood pressure monitoring device. A total of 24 practices volunteered for participation and fulfilled the inclusion criteria. These practices were randomized in two study arms of equal size. All participating physicians are asked to sign an informed consent form. Patients are recruited by these physicians.

### Inclusion and exclusion criteria for patients

Patients are eligible for recruitment if 1) they are ≥18 years old and 2) their blood pressure is uncontrolled according to current guidelines: ≥140/90 mmHg in office readings, and/or ≥130/80 mmHg in 24-hour ambulatory measurements (based on the average 24-hour blood pressure), and/or ≥135/85 mmHg in patient self-measurements at home (based on the mean of a one-week protocol with at least two measurements daily) [7]. Patients with and without hypertension-related diseases such as angiographically proven coronary disease, peripheral or cerebral vascular disease, and/or high risk conditions such as diabetes can be recruited. All patients must be able to give informed consent and to read and comprehend the German language. Patients fulfilling all of these criteria are asked for study participation, receive written information about the study, and sign an informed consent form. A total of 169 patients were enrolled at baseline; of these, 101 (59.8%) were associated with the intervention arm.

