### Outcome measures

The primary endpoint of the study is the change of the blood pressure control rate, defined as percentage of patients with an average 24-hour blood pressure <130/80 mmHg. The key secondary endpoints are the changes in average systolic and/or diastolic blood pressure (in mmHg) and changes in practice-specific hypertension management stratified by the intervention status of the practice. All outcomes are measured at baseline (before the intervention) and at follow-up (3 months after the last education session) in both study arms. This results in an average follow-up period of 5 months per patient.

To determine the interventional effectiveness on the patients’ level, each study patient receives a 24-hour ambulatory blood pressure monitoring at baseline and at follow-up. To control for confounding, general practitioners complete a questionnaire on medical characteristics of each study patient (for example, diagnosis, comorbidities, medication, and differential diagnoses). Study patients complete a self-administered paper and pencil questionnaire on individual characteristics such as sociodemographic characteristics, risk factors (for example, physical activity and smoking behavior), medication adherence, and management of blood pressure self-readings at baseline and follow-up.

At baseline, general practitioners complete a questionnaire on personal characteristics (age, sex), medical degree(s), additional qualifications, and individual attitudes toward hypertension treatment (motivation and self-efficacy). To determine practice changes after intervention, the follow-up questionnaire focuses on changes in daily practice routines and determines which of the hypertension management strategies are implemented by the practices.

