### Statistical hypotheses, methods, and analyses

The primary endpoint (differences in the blood pressure control rate between intervention and control group) will be analyzed using a chi-square test. A *P* value <0.05 will be considered significant.

For analyses of secondary endpoints, average blood pressure levels at baseline and at follow-up will be determined for all study patients and separately for patients of both study arms. Differences between baseline and follow-up will be tested for significance within each study arm using paired t-tests. Differences in the mean systolic and diastolic blood pressure level of patients of the intervention group and patients of the control group will be tested for significance using an adjusted t-test for independent samples, which accounts for the intra-cluster correlation [6].

The analysis will determine which elements of hypertension management have been implemented into everyday routine during the study period and which of them are regarded as being helpful. To describe the effect of single hypertension management strategies on blood pressure, bivariate analyses will be conducted.

A generalized linear mixed model will be performed to identify predictors on blood pressure control at follow-up. The model will include patient level covariates such as age, sex, lifestyle, comorbidities, and changes in each patient’s hypertension management as well as cluster-level covariates such as changes of hypertension-related diagnostic and therapeutic strategies. Modeling will account for cluster effects by random effects modeling. Statistical analyses will be performed using IBM SPSS Statistics for Windows, Version 22.0 (Armonk, New York: IBM Corp.).

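### Physicians of randomised practices recruited the patients, apparently after allocation, enrolment was uneven (101 v 68), and the primary chi-square test adjusts for no baseline value

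*Protocol article*

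**What the plan says.** **Allocation and recruitment.** Under Practice and patient recruitment, 24 volunteering practices met the criteria. The article continues: "These practices were randomized in two study arms of equal size". After a sentence on physician consent it adds: "Patients are recruited by these physicians". It gives no date for randomisation and does not say whether recruiters knew their allocation.

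**Entry and enrolment.** Under Inclusion and exclusion criteria for patients, blood pressure counts as uncontrolled at "≥140/90 mmHg in office readings, and/or ≥130/80 mmHg in 24-hour ambulatory measurements", or on home readings, again joined by and/or. Patients who meet all criteria are to be asked to take part. Enrolment is then given: "A total of 169 patients were enrolled at baseline; of these, 101 (59.8%) were associated with the intervention arm". Under Study design: "Each practice cluster includes five patients at minimum".

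**Endpoint and data.** Under Outcome measures: "The primary endpoint of the study is the change of the blood pressure control rate", with control meaning an average 24-hour pressure below 130/80 mmHg. Every patient has 24-hour monitoring at baseline and at follow-up. The same section adds: "To control for confounding, general practitioners complete a questionnaire on medical characteristics of each study patient".

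**Analysis.** The section Statistical hypotheses, methods, and analyses names the main test as follows: "The primary endpoint (differences in the blood pressure control rate between intervention and control group) will be analyzed using a chi-square test". No baseline value or covariate is named. A generalized linear mixed model is planned separately, to find predictors of control at follow-up. It has random cluster effects, and its covariates include changes in each patient's management.

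**The concern.** Randomising practices balances practices in expectation. It balances patients only if the way patients enter does not depend on the arm. Physicians who know their arm and choose whom to approach can, without intending it, enrol different kinds of patient. Unequal numbers per practice are one visible sign that this may have happened.

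The entry rule makes this matter for the endpoint itself. A patient who qualifies on an office or home reading alone can have a 24-hour pressure below 130/80 at baseline, and so already counts as controlled. If the share of such patients differs between arms, the follow-up control rates differ with no intervention effect. Correcting the test for clustering widens the standard error but does not remove this shift. The baseline 24-hour reading would remove much of it, and it exists for every patient, but the stated primary test does not use it.

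**Working it through.** **1. The enrolment figures.** 101/169 = 59.8%, as stated. Control: 169 − 101 = 68. Per practice: 101/12 = 8.4 and 68/12 = 5.7. At the five-patient minimum each arm would have 12 × 5 = 60, so intervention practices added 41 beyond it and control practices 8.

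**2. How unusual the split is.** An exact binomial test of 101/169 against 0.5 gives p = 0.014, but it treats patients as having been allocated independently. The unit is the practice, so the better check is t = (101/12 − 68/12) / (SD × √(2/12)) on 22 degrees of freedom, where SD is the between-practice SD of cluster size. The article does not give this SD, so a range is assumed:

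| Assumed SD | t | p |
|---|---|---|
| 2 | 3.37 | 0.003 |
| 3 | 2.25 | 0.035 |
| 4 | 1.68 | 0.11 |
| 5 | 1.35 | 0.19 |

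The split may or may not be beyond chance.

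**3. Shift if the arms differ at baseline.** Assumptions: no treatment effect; intervention patients enter d SD lower on 24-hour pressure; baseline to follow-up correlation 0.6. The 35% follow-up control rate is the control-arm figure in Sample size calculation.

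Follow-up-only comparison: Φ(z(0.35) + 0.6d) − 0.35, with z(0.35) = −0.385.
- d = 0.2: Φ(−0.265) − 0.35 = +4.5 points.
- d = 0.3: Φ(−0.205) − 0.35 = +6.9 points.

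Comparison of changes: subtract the baseline difference, Φ(z(b) + d) − b, where b is the share of control patients already controlled at baseline. The article does not give b, so it is assumed:

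| b | Bias in change, d = 0.2 | Bias in change, d = 0.3 |
|---|---|---|
| 5% | +2.1 | +2.9 |
| 10% | +0.6 | +0.6 |
| 15% | −0.6 | −1.2 |
| 25% | −2.2 | −3.5 |

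The two readings of the endpoint therefore carry different biases, possibly of opposite sign.

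**4. Effect on the test.** Null trials were simulated with 12 + 12 practices, 101 v 68 patients, ICC 0.05 (the article's value) and an assumed follow-up control of 70% if controlled at baseline and 30% if not. The chi-square test on follow-up control is set against a linear model with arm and baseline control and cluster-robust standard errors:

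| Controlled at baseline, intervention v control | Chi-square: bias, rejection | Adjusted: rejection |
|---|---|---|
| 15% v 15% | about 0, 8.3% | 5.6% |
| 25% v 15% | +3.9 points, 11.9% | 6.1% |
| 30% v 10% | +8.0 points, 21.2% | 5.5% |
| 10% v 30% | −8.0 points, 21.7% | 6.0% |

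The adjusted bias is about 0 throughout. The biases agree with direct arithmetic: (0.25 − 0.15) × (0.70 − 0.30) = 4.0 points, and 0.20 × 0.40 = 8.0. The 8.3% in the first row comes from ignoring clustering, which is a separate matter. Only the excess above it belongs to this point.

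**The case against.** Several stronger readings are tempting, and the article does not support them.

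- *That trained practices drew in milder or more motivated patients.* Baseline precedes the intervention, so no practice had been trained when it enrolled. At most its physicians knew their allocation, and the article does not say that they did.
- *That recruitment certainly followed randomisation.* This is the plain reading of the order of the text, but no dates are given. A condensed article may leave timing and concealment to a fuller document.
- *That nothing governed whom to approach.* The article says that eligible patients are asked. What it does not describe is consecutive or random sampling.
- *That 101 v 68 proves selection.* Practice size could explain it, and unequal counts do not show unequal composition.
- *That the whole 4.5 to 6.9 points enters the result.* This requires a follow-up-only comparison and an assumed direction. Outcome measures calls the endpoint a change, and a comparison of changes would shift less and could reverse.
- *That the confounder data go unused.* The mixed model uses age, sex, lifestyle and comorbidities.

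All of this limits the claim. It does not supply an adjusted primary comparison. The analysis section shows no baseline term for the change. The mixed model is a search for predictors: it names neither study arm nor baseline pressure, and it includes management changes made after randomisation, which may lie on the path of the effect. It cannot stand in for an adjusted primary test.

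**Conclusion.** The point holds as a weakness in the stated primary analysis, not as a demonstration of bias. Three features combine: recruitment by physicians of randomised practices, apparently after allocation; uneven enrolment; and an entry rule that lets the arms differ on the endpoint at baseline. The stated primary test has nothing to absorb such a difference.

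The size depends on assumptions that the article cannot settle: the extent and direction of selection, the correlation of 0.6, the share controlled at baseline, and whether follow-up rates or changes are compared. Under 0.2 to 0.3 SD of selection, the bias is 4.5 to 6.9 points on follow-up rates and between +2.9 and −3.5 points on changes for baseline control of 5% to 25%. Selection in the opposite direction would hide a benefit. In the simulated scenarios, baseline adjustment with cluster-robust errors brought the bias to about zero and false rejection to 5.5% to 6.1%, but there selection acted only on the measured baseline status.

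**What to change.** Before the arms are compared:

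1. Make the primary analysis a model of 24-hour blood pressure control at follow-up that accounts for clustering. Include study arm, baseline 24-hour systolic and diastolic pressure, and a short prespecified set of baseline covariates: age, sex, and diabetes or vascular disease. Leave out management changes after randomisation. This also settles how baseline enters an endpoint described as a change in one section and tested as a group difference in another.
2. Report baseline characteristics by arm, including the share already below 130/80 mmHg on 24-hour measurement.
3. State the order of randomisation and recruitment, and whether recruiters knew their allocation. If recruitment came second, name it as a limitation.
4. Say that adjustment removes only selection on measured factors.
5. Use the qualifying criterion (office, 24-hour or home) as a covariate, or the first five patients per practice as a sensitivity set, only if those data were recorded; the article lists neither. The sensitivity set would keep at most 120 patients and drop at least 49. It equalises numbers but does not remove selection, because the first five can be chosen too.

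The cost is analysis wording and a few sentences of reporting. The core model needs no new measurement, because baseline 24-hour pressure and patient characteristics are already collected. Trial status describes follow-up as complete and data management as ongoing, so the design can no longer change but the analysis can.

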### Outcome measures

The primary endpoint of the study is the change of the blood pressure control rate, defined as percentage of patients with an average 24-hour blood pressure <130/80 mmHg. The key secondary endpoints are the changes in average systolic and/or diastolic blood pressure (in mmHg) and changes in practice-specific hypertension management stratified by the intervention status of the practice. All outcomes are measured at baseline (before the intervention) and at follow-up (3 months after the last education session) in both study arms. This results in an average follow-up period of 5 months per patient.

To determine the interventional effectiveness on the patients’ level, each study patient receives a 24-hour ambulatory blood pressure monitoring at baseline and at follow-up. To control for confounding, general practitioners complete a questionnaire on medical characteristics of each study patient (for example, diagnosis, comorbidities, medication, and differential diagnoses). Study patients complete a self-administered paper and pencil questionnaire on individual characteristics such as sociodemographic characteristics, risk factors (for example, physical activity and smoking behavior), medication adherence, and management of blood pressure self-readings at baseline and follow-up.

At baseline, general practitioners complete a questionnaire on personal characteristics (age, sex), medical degree(s), additional qualifications, and individual attitudes toward hypertension treatment (motivation and self-efficacy). To determine practice changes after intervention, the follow-up questionnaire focuses on changes in daily practice routines and determines which of the hypertension management strategies are implemented by the practices.

### Intervention group

General practitioners of the intervention group participate in a modern education on strategies of structured hypertension management in primary care. It is conducted as an in-class, three-session medical education program. Central elements of the education are 1) training on valid upper arm blood pressure readings; 2) evidence-based information on resistant hypertension, secondary hypertension, and modern pharmacotherapy, in the form of presentations and group discussions of actual cases; and 3) the introduction and distribution of practice tools to facilitate the long-term implementation of hypertension management. The following practice redesign tools are provided in print and electronic versions:current hypertension guidelines [7],10-step checklist how to obtain standardized upper arm office blood pressure readings according to guidelines [7],template of a blood pressure documentation sheet for serial documentation of blood pressure values by patients,list of electronic blood pressure devices that carry the quality seal of the German Hypertension League,prescription template detailing how to prescribe an electronic blood pressure device,prescription template detailing how to prescribe relaxation training programs (progressive muscle relaxation and autogenous training),checklists to assist in the diagnosis of secondary hypertension,templates for specialist referral sheets for the work-up of secondary hypertension,overview sheet specifying the mechanism of action of the various antihypertensives,information sheets on blood pressure lowering effects (in mmHg) of different single and combined blood pressure lowering measures such as regular physical activity or intensified pharmacotherapy [3], andpatient information leaflet about hypertension.

All information sheets are written in an easily understandable language and designed in a clear layout so that they can be used for patient information and education. General practitioners and practice assistants participate in the session on blood pressure measurements, while all other sessions are offered to physicians only. The education sessions are supported by hypertension specialists from the German Hypertension League.

Participating general practitioners are free in their choice of diagnostic and therapeutic strategies. Patient responsibility remains solely in the hands of the general practitioner in charge. Due to the physician-centered approach, study patients receive an indirect intervention.

